### 6.4 Pre Study Results

1) Double-blind, randomized, double-blind, placebo-controlled clinical trials to assess the effect of 8 weeks of poly-gamma-glutamate on human immunity enhancement, The Catholic The Catholic University, Korea Seoul St Mary’s Hospital

- A total of 99 patients were enrolled in this study. The study included 33 patients with low-dose gamma glutamic acid (500 mg), 33 patients with high-dose gamma glutamic acid (1000 mg), and 33 patients with placebo. To compare the difference in the mean cytotoxicity of natural killer cells between the three groups, the mean changes in the cytotoxicity of natural killer cells at baseline and at each time point (4 weeks, 8 weeks) Using the Kruscal-Wallis test based on the normalization of the p values <0.05 was considered statistically significant.

- The mean changes in the cytotoxicity of natural killer cells at each time point (4 weeks, 8 weeks) compared to baseline were 0.5 ± 3.5% (increase rate: (P <0.05). There was a statistically significant difference between the two groups (4.5%, 4.3%, and 39.1%, respectively) 0.0174). Multiple comparisons showed that p-value = 0.0013 in the low-dose and high-dose groups, high-dose and placebo groups. As a result of multiple comparisons, there was a statistically significant difference in the change of cytotoxicity between the low dose group and the high dose group, the high dose group and the placebo group, and the cytotoxicity increase rate in the high dose group was higher than that in the low dose group and the placebo group.

- Phenotypic changes of peripheral blood mononuclear cells (MHC class II) by secondary efficacy: The CD8, CD4, CD8, CD14, and CD56 groups were compared between the three groups. , And the CD56 item was statistically significant (p-value = 0.0157, p-value = 0.0002) at the 4th and 8th weeks of the baseline, respectively. The results of multiple comparisons showed that the two items (CD8, CD56) showed different amounts of change in the low dose, high dose, high dose and placebo groups. In the safety evaluation, no patients were clinically withdrawn due to adverse events, and no serious adverse events were observed. There was no significant difference between the three groups in blood pressure and pulse, and no abnormality was found on laboratory examination

2) Randomized, placebo-controlled, single-dose/repeat-dose, phase-I clinical trials to assess safety, tolerability and pharmacokinetic characteristics after oral administration of poly-gamma glutamic acid in healthy male clinical trial subjects.

- When poly-gamma glutamic acid was orally administered to healthy male volunteers, it showed safety and tolerability up to 3.0gram/day.

## [7] Investigational Product Information

### 7.1 Investigational Product Information

#### Test: PGA

• Product Code : BLS-PGA

• Properties and Formulation : Brown glass bottle with clear viscous syrup

• Storage Method : Refrigerated storage (2 ℃ ~ 8 ℃), airtight container

• Expiration date : 24 months from date of manufacture

#### 7.1.2 Control: Placebo

• Properties and Formulation : Brown glass bottle with clear viscous syrup

• Storage Method : Refrigerated storage (2 ℃ ~ 8 ℃), airtight container

• Expiration date : 24 months from date of manufacture

### 7.2 Method of administration of Investigational Product

Administered once daily

### 7.3 Packaging and Labeling

#### 7.3.1 Packaging of Investigational Product

It is a bottle containing liquid formulation and packed in 100mL unit which can be taken once.

To avoid distinction between the test drug and the reference drug, the drug should be packed in a brown glass bottle of the same outline in the same volume to maintain double-blindness.

The payment package at the time of dispensing the clinical trial drug will include an extra five days for four weeks.

#### 7.3.2 Labeling of Investigational Product

1) Marked as “Investigational Product”

2) Investigational Product Code

3) Expiration date

4) Storage Method

5) Name and address of the person who has been approved for the Study plan

6) Marked as “Can’t be used for purposes other than study”

### 7.4 Management and Storage of Investigational Product

#### 7.4.1 Archive / Distribution / Management of Investigational Product

The Principal Investigator is responsible for ensuring that the Investigational Product received from the applicant is correctly received by the person in charge and kept in a safe place and that the Investigational Product is not damaged before the grant. The Investigational Product used in this study shall be controlled not to be used for purposes other than clinical studies. The management pharmacist must record the actual temperature using a graduated thermometer or thermocouple during storage, and record the measured temperature at least on the working day in the journal. If there is a temperature drift that is outside the acceptable range, you must contact your monitor. The temperature log should be kept in the laboratory laboratory file after the clinical trial is terminated.

The sponsor should check the quantity and storage status of the Investigational Product during the clinical trial and make sure that the clinical trial is conducted properly.

Each individual clinical trial subject package shall be delivered as provided by the sponsor without additional repackaging or labeling at the testing laboratory.

#### 7.4.2 Return of Investigational Product

The sponsor shall withdraw and discard the unused Investigational Product if the clinical trial is discontinued or terminated or if the clinical trial manager fails to conduct the test according to the plan. At this time, the Investigational Product Manager must return the unused Investigational Product to the sponsor after the consultation with the test manager and preserve the certificate. Returned Investigational Products are either disposed of or disposed of in accordance with the requirements of the applicant's company.

## [8] Indications

### Cervical Intraepithelial Neoplasia (CIN I)

According to the American Society of Colposcopy and Cervical Pathology (ASCCP) Consensus Guidelines in 2006, CIN Ⅰ diagnosed in women undergoes routine observation without treatment.[5]

## [9] Inclusion/ Exclusion Criteria, Sample Size

### Inclusion criteria

You may participate in this study only if all of the following criteria are met:

1. Fertile female aged between 20 and 49

2. Subjects who are diagnosed as Cervical intraepithelial neoplasia 1 (CIN1)

3. Subjects who are infected with HPV (Human Papilloma Virus) positive (+)

4. White Blood Cell Count(WBC) over 4 10^3^/ul, Hemoglobin above over 9.0g/dL Platelet over 150 10^3^/uL and ANC (Absolute Neutrophil Count) over 1,500 10^6^/L

5. AST (Aspartate Aminotransferase) no less than 4 times higher than normal ALT (Alanine Aminotransferase) no less than 4 times higher than normal

6. Normal for EKG (Electrocardiography) and no active disease detected trough chest X-ray

7. Be informed of the nature of the study and will give written informed consent

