### Exclusion criteria

If any of the following criteria are met, you will not be able to participate in this study:

1. Malignant tumor in any organ other than cervical intraepithelial neoplasia

2. Active liver disease, immune disorder and severe renal failure

3. Leukemia, collagenosis, sclerosis, autoimmune disease, clinically significant allergic disease (mild allergic symptom not required medicine excluded)

4. Diagnosed diabetes

5. Taking any of followings affecting immunological reaction within 7 days (Glucocorticoid, vitamins, health food and oriental medicine etc)

6. Pregnancy and breastfeeding

7. Registered in other clinical trials

8. Patients whom the investigator considers inappropriate to participate in the study

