#### Visit 1(Within -4 weeks, Screening)

If you want to participate in the clinical trial after receiving explanation of this study, write down the written consent of the patient to be tested and perform the screening procedure and examination described below. Those with clinically significant anomalies are excluded from clinical trials.

1) Written consent of clinical trial patients

2) Demographic information

3) Examination of medical history (within 2 years of related disease, within 6 months of other diseases), taking medication survey (within 4 weeks)

4) signs of vitality, physical examination, physical measurement (weight, height)

5) Laboratory test, pregnancy test

6) Electrocardiography

7) Chest X-ray examination

8) Colposcopy (Reid's Index, Biopsy)

The test result within 4 weeks before acquisition of the consent is recognized as screening test.

(However, when using the results of other institutions, the results of biopsy should be secured so that the results can be confirmed at least.)

9) Pap smear test, HPV DNA test, Hybrid Capture II assay

10) Conformity Assessment of Clinical Test Subject (Selection / Exclusion Criteria)

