**14.2 Analysis exclusion criteria**

In case of a violation of a critical clinical trial plan, the patient should be excluded from the PP analysis.

1) If the patient's compliance with the Investigational Product is less than 80%

2) In case of violation of selection criteria and exclusion criteria during the test

3) In combination with drugs that may affect the efficacy evaluation

4) When the validity evaluation item inspection (visit 1) is not carried out

5) If you visit due to visiting date

Other violations of the clinical trial protocol, which are considered to have no effect on the interpretation of the study results, must be clearly stated in terms of the violation or delay and the reason and the researcher, sponsor, monitor personnel and statisticians and to include them in the PP analysis.

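### Inclusion item 5 sets a minimum, not a maximum, for AST and ALT, and so conflicts in practice with the liver disease exclusion and the screening rule

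*Protocol*

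**What the plan says.** Section 9 of the protocol opens its inclusion list with the rule "You may participate in this study only if all of the following criteria are met". Item 5 of that list reads "AST (Aspartate Aminotransferase) no less than 4 times higher than normal ALT (Alanine Aminotransferase) no less than 4 times higher than normal". The Protocol Outline carries the same item in the same words, and no other part of the protocol states a different AST or ALT limit.

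Three other provisions bear on the same women:

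- Exclusion item 2, in both the Outline and section 9, removes women with "Active liver disease, immune disorder and severe renal failure". It gives no enzyme threshold.
- The screening visit (section 12.3, Visit 1), which includes laboratory tests, adds "Those with clinically significant anomalies are excluded from clinical trials". Section 12.2.4 lists AST and ALT among the laboratory tests.
- Section 14.2 names as a ground for leaving the per-protocol (PP) analysis "In case of violation of selection criteria and exclusion criteria during the test". Section 14.1 lists a breach of the selection or exclusion criteria among the events that can lead to stopping or dropout.

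**The concern.** The phrasing of item 5 fixes a floor. Its neighbours select for health: item 4 sets minimum blood counts, and item 6 asks for a normal ECG and a chest X-ray without active disease. Item 5 alone makes an abnormal result a condition of entry.

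Two things are at stake. First, a mandatory eligibility rule with a safety purpose cannot sensibly be followed as written, because it turns away women with normal enzymes and passes only women whom other rules would be expected to remove. Second, if sites at the six participating hospitals read it the other way without a documented change, they enrol women who breach the written text. Those breaches feed into the dropout rule and the PP definition. Section 21.8 does not allow departures from the signed protocol without prior agreement between the researcher and the sponsor, medical emergencies aside, so quiet reinterpretation at a site is not a clean way out.

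**Working it through.** The protocol gives no figure to reproduce, and no formula applies. The check sets the provisions side by side.

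**Step 1: the rule in logical form.** All inclusion items must hold, so item 5 requires AST at or above 4 times normal AND ALT at or above 4 times normal. There is no upper bound on either.

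**Step 2: apply it to the possible screening results.**

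| Screening result | Item 5 as written | Other provisions | Outcome on the text |
| --- | --- | --- | --- |
| AST and ALT both normal | Not met | None triggered by the enzymes | Ineligible |
| At least one enzyme raised, but at least one below 4 times normal | Not met | Depends on clinical judgement | Ineligible |
| Both enzymes at or above 4 times normal | Met | Exclusion 2 (active liver disease) or the Visit 1 rule on important abnormal findings would be expected to apply | Expected to be excluded |

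The first two rows are certain from the text. The third is an expectation: exclusion 2 has no numerical threshold, and the Visit 1 rule turns on clinical significance. Few or no women are therefore clearly eligible, but the text does not make the set logically empty.

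**Step 3: look for a correction elsewhere.** The Outline and section 9 agree word for word, so neither can be used to correct the other. Section 12.2.4 names the tests without limits.

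**Step 4: the consequence if sites read the line the other way.** A woman breaches item 5 as written if either enzyme is below 4 times normal. Let q be the share of enrolled women for whom that is so. With 200 planned, the number in breach is 200 × q. The protocol gives no enzyme distribution, so q is an assumption. If it is most of them, q lies between one half and one, and the count lies between 200 × 0.5 = 100 and 200 × 1 = 200. The upper end is the more plausible for a population screened on blood counts, ECG and chest X-ray, but that is a judgement and not a figure in the protocol.

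**Step 5: trace the breach into the analysis sets.**

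- *Dropout (14.1):* the listed events can be grounds, so the rule is permissive.
- *PP (14.2, item 2):* a breach of selection criteria removes the woman from PP on a literal reading. The item speaks of violation during the test, so whether it covers a breach already present at entry is not fully clear.
- *ITT (15.3.2):* all randomised women who took study drug at least once. An eligibility breach removes nobody, and the final evaluation follows this set.
- *Knock-on:* section 15.3.2 has every efficacy analysis run in both ITT and PP, with further exploration if they differ. A PP set thinned by a wording error would make that comparison uninformative.

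**The case against.** The strongest reply is that no one will be misled. The adjoining items plainly select healthy women, and the English is visibly a rough translation: Korean text remains in the sample size table, and the t-test appears under a garbled name. A slip in translation is plausible. This lowers the likely impact. It does not repair the text, because the original is not shown, the wording appears twice in an operative criterion, and a reader who guesses the direction still cannot confirm that the multiple is right. For the same reason, to call the criterion inverted is an inference about intent. What the text supports is that it sets a minimum.

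A reader might also infer three stronger things that the protocol does not support:

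- *That item 5 and exclusion 2 cannot both be applied.* Active liver disease is not defined by an enzyme level, so a woman could in principle satisfy item 5 without meeting exclusion 2. The rule at Visit 1 makes the tension sharper, but it too rests on judgement.
- *That women with markedly raised enzymes will be given the product.* That would need exclusion 2, the Visit 1 rule, the investigator's discretion under exclusion 8 and the final eligibility review at Visit 2, which uses clinical test results, all to fail. The more realistic result is a criterion that cannot be enforced, with deviations on paper.
- *That the primary result is compromised.* ITT decides the trial, and eligibility breaches do not change who is in it.

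**Conclusion.** The point holds as an internal inconsistency in an eligibility rule that is wrong as written. Item 5 demands raised AST and ALT as a condition of entry, bars women with normal enzymes, and conflicts in practice with exclusion 2 and the screening rule at Visit 1. Nothing elsewhere in the protocol corrects it.

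Its effect on the analysis is confined to the PP set and to the dropout rule. It arises only if sites depart from the literal text, and for PP only on a literal reading of section 14.2. Its size, somewhere between half and all of the 200 planned women, rests on an assumption about enzyme levels that the protocol does not supply. The defect itself does not depend on that assumption. The case for correcting the line before the protocol is used rests on the mandatory wording alone, not on a projected harm to patients or damage to the primary comparison.

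**What to change.** Reconcile inclusion item 5, in both the Protocol Outline and section 9, with exclusion item 2 (also in both places) and with the exclusion of clinically important abnormal findings at Visit 1. The sponsor's medical lead should confirm the direction of the limit and its value; neither is proposed here.

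Treat the edit as a change in patient selection criteria under section 21.7, which requires approval, and not as the minor rewording that the same section exempts. Record the date, reason and detail of the revision, as that section asks. If any eligibility form has already been prepared from this line, check it against the corrected text.

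The cost is one line changed in two places plus the approval step. Sample size, endpoints and the definition of the ITT set do not change.

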### Exclusion criteria

If any of the following criteria are met, you will not be able to participate in this study:

1. Malignant tumor in any organ other than cervical intraepithelial neoplasia

2. Active liver disease, immune disorder and severe renal failure

3. Leukemia, collagenosis, sclerosis, autoimmune disease, clinically significant allergic disease (mild allergic symptom not required medicine excluded)

4. Diagnosed diabetes

5. Taking any of followings affecting immunological reaction within 7 days (Glucocorticoid, vitamins, health food and oriental medicine etc)

6. Pregnancy and breastfeeding

7. Registered in other clinical trials

8. Patients whom the investigator considers inappropriate to participate in the study

### 9.3 Sample size

#### 9.3.1 Sample size

##### - Total 200 patients (PGA Group 100 patients, Placebo Group 100patients)

Based on published literature, we assumed that 31% of the cases of CIN 1 would resolve spontaneously, and a clinically significant difference was estimated at 20%. 80 patients per group.

| Group | Dose | Patient | Expected response Rate | Expected response patient | Duration of treatment/Observation |
| --- | --- | --- | --- | --- | --- |
| Placebo | - | 80 | 31% | 24.8 | administered once daily for 4 weeks /  observation for 8 weeks |
| PGA | 1,500mg/day | 80 | 51% | 40.8 |  |
| Total | - | 160 |  |  |  |

Cervical intraepithelial neoplasia (CIN I) can act as a precursor to invasive cervical cancer and is the most common significant gynecologic disease in women of reproductive age. study, we investigated clinical efficacy and immune response of oral administration of γ-PGA from women with cervical intraepithelial neoplasia 1 (CIN 1) in phase 2b study

H_0_ : p_1_≦p2 vs. H_1_ : p_1_>p_2_

p_1_ : Response rate of treatment, p_2_: Response rate of Control

Expected response rate: PGA Group: 81%, Control Group: 51%

significance level : 0.05, statistical power : 80%, one-sided test

The Sample size is total 160 patients, 80 patients per group when the Single stage method.

If 20% drop out is considered, the sample is total 200 patients, 100 patients per group

The sample size is according to the Two stage optimal design (Jung(2008)) Method is shown in the following table.

[Jung(2008) Two-stage]

| Stage | Patient | Difference between two groups (Treatment patient-Control patient) | 제 significance level, statistical power |
| --- | --- | --- | --- |
| 1  2 | 43  80(43+37) | +2  +11 | 0.461, 0.800 |

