###### 9.3.2 Basis of calculation

The prevalence of Cervical intraepithelial neoplasia (CIN I) in the Korean population is very limited, and there is little clinical study on the efficacy of the treatment [6]. In this study, To investigate the effect of glutamic acid, we refer to the results of research abroad.

Most of the studies on natural cure rates for Cervical intraepithelial neoplasia (CIN I) were done for more than 6 months. The natural cure rates at 3 months as in the present study were compared with those of CIN I and II (Barnett et al. As a result of the study, about 31% in the placebo group and about 33% in the photodynamic therapy (PDT).[8] A 15-week study of Trimble (2005) with CIN II and III showed a natural cure rate of 28%. [9]

In a study by Bansal et al. (2008), who conducted a cohort study, the study included 1001 CIN I patients who were followed up for at least 12 months to determine the natural cure rate at the 6-month follow-up, approximately 49% of the patients were reported to return to normal. [10]

In a phase 2 clinical trial (Hefler et al., 2010) to confirm the effect of topical infusion of progesterone in a similar clinical trial phase, the natural cure rate of the control group without special treatment was 38.8% of 96 patients. [11]

Based on the results of the above studies, it can be summarized that most of the natural cure rates are within 3 months and the additional effect after 3 months is about 7.8% ~ 18.0%. The natural cure rate at 3 months was set at 31.0%.

This study was established as an exploratory study with phase 2 clinical studies and it was concluded that at least 20% of the effects of high natural healing rates should be clarified to enable large scale clinical studies. Was not worth it.

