**[11] Study Methodology**

The purpose of this study was to investigate the effect of oral administration of poly-gamma glutamic acid (γ-PGA) on the Cervical Intraepithelial Neoplasia (CIN I) Double-blind, placebo-controlled study designed to identify immunomodulatory effects by assessing changes in immunological parameters.

In this study, a total of 80 patients (100 patients in the case of dropout) were participated in the study. Participation in the study was conducted in two stages as proposed by Jung (2008). In the first stage, 43 subjects were recruited in each group, and the main effect variable, healing, was checked. The difference in the number of subjects in the clinical trial for healing was less than 2 (the number of subjects who were treated for healing of poly-gamma glutamic acid - The number of subjects in clinical trials), it is judged that there is no effect of poly-gamma glutamic acid on cervical epithelial dysplasia and the study is terminated.

If there is more than one difference in step 1, we will consider a two-step study design that will enter step 2 and add an additional 37 patients per group. If the difference in the number of subjects in the clinical trial between group 1 and group 2 of 80 patients in each group is greater than 11 patients, the effect of γ-PGA will be confirmed. Otherwise, γ-PGA. It will be judged that it is not effective in healing the injured Cervical Intraepithelial Neoplasia (CIN I).

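### Section 9.3.1 misprints two design figures: expected rates of 81% vs 51% (its own basis is 51% vs 31%) and a significance level of 0.461 (the rule's exact maximum is 0.0461)

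*Protocol*

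**What the plan says.** Section 9.3.1 (Sample size) gives the basis of the calculation: "we assumed that 31% of the cases of CIN 1 would resolve spontaneously, and a clinically significant difference was estimated at 20" percent. Its table agrees, with rows "Placebo | - | 80 | 31% | 24.8" and "PGA | 1,500mg/day | 80 | 51% | 40.8" (group, dose, patients, expected rate, expected responders). Section 9.3.2 supports the control figure: "The natural cure rate at 3 months was set at 31.0" percent.

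Directly under the hypotheses, section 9.3.1 then lists "Expected response rate: PGA Group: 81%, Control Group: 51" percent, followed by "significance level : 0.05, statistical power : 80%, one-sided test". The two-stage table below gives 43 and then 80 (43+37) patients per group, boundaries +2 and +11, and a significance level and power of 0.461 and 0.800. The Sample Size row of the Protocol Outline repeats all of this, including both the 31%/51% table and the 81%/51% line.

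Three other places bear on the point:

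- Section 15.3.4 continues to stage 2 at a difference of two or more. It calls a final difference below 11 a failure, but words success as more than 11. The Outline's statistical analysis row does the same for the final boundary, so a difference of exactly 11 is left unassigned in both.
- Section 11 requires a final difference greater than 11.
- Section 11 also says: "In this study, a total of 80 patients (100 patients in the case of dropout) were participated in the study". Section 9.3.1 gives 160 in total, and 200 with dropout.

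**The concern.** One section carries two sets of hypothesis inputs. They differ in control rate (31% or 51%) and in target difference (20 or 30 points). It also carries two significance levels, 0.05 and 0.461. These figures tell a reader what effect the trial was sized to detect and what false-positive risk it accepts. Sections 15.3.1 and 15.3.4 rest the primary conclusion on this design and promise a p-value from its significance-level formula. Someone who takes the printed inputs at face value cannot reproduce 80 per group, and would misreport the assumed placebo rate.

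**Working it through.** **Inputs.** From 9.3.1: one-sided 0.05, 80% power, 1:1 allocation, stage sizes 43 and 37 per group, boundaries +2 and +11, and rate pairs 51/31 and 81/51. From 15.3.4: continue if D1 ≥ 2; failure if D < 11, hence success if D ≥ 11. D1 and D are PGA responders minus control responders at stage 1 and overall.

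**1. The plan's own figures at 51% vs 31%.** Expected responders are 80 × 0.31 = 24.8 and 80 × 0.51 = 40.8, as in the table. Dropout inflation is 80/(1 − 0.20) = 100 per group, also as stated.

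For the two-stage rule the exact probability of success is

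P(success) = Σ over d ≥ 2 of P(D1 = d) × P(D2 ≥ 11 − d),

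where D1 is a difference of two binomials of size 43 and D2 a difference of two binomials of size 37.

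| True rates (PGA / control) | P(success) |
| --- | --- |
| 50 / 50 | 0.0461 (maximum over common rates) |
| 31 / 31 | 0.0348 |
| 51 / 31 | 0.805 |
| 60 / 40 | 0.80003 |
| 81 / 51 | 0.989 |

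So 51/31 matches the stated 80% power, and the rule's largest type I error is 0.0461. The printed 0.461 is ten times that.

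**2. Single-stage size for each pair.** The pooled normal formula is

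n = [1.645·√(2p̄(1−p̄)) + 0.842·√(p1(1−p1) + p2(1−p2))]² / (p1−p2)².

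- 51/31: p̄ = 0.41, so n = [1.645·√0.4838 + 0.842·√0.4638]²/0.04 = 73.7, i.e. 74 per group (84 with continuity correction). The exact binomial-difference test, with alpha held at or below 0.05 at a common rate of 50%, needs 78 per group (boundary 11, power 0.802). At 80 per group with boundary 11, alpha is 0.0483 and power 0.817.
- 81/51: p̄ = 0.66, so n = [1.645·√0.4488 + 0.842·√0.4038]²/0.09 = 29.8, i.e. 30 per group (37 with continuity correction). The exact test needs 36 per group.

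The stated 80 lies close to the 51/31 results and is more than twice any one-sided 81/51 figure found here.

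**3. Could 0.461 be some other quantity?** The chance of passing stage 1 under the null, P(D1 ≥ 2), is 0.363 at a common 31% and 0.373 at a common 50%. Neither is 0.461. A misplaced decimal in 0.0461 is the simplest reading.

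**4. Dependence on the final boundary.** Reading success as D > 11 (section 11), and keeping D1 ≥ 2, maximum type I error is 0.033 and power at 51/31 is 0.762. The printed power therefore holds only with D ≥ 11.

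**5. Total.** 2 × 80 = 160 and 2 × 100 = 200, as in 9.3.1. Section 11's own later text speaks of 80 in each group, which contradicts its total of 80.

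**The case against.** The best defence is that nothing real is broken. The intended assumption can be recovered: the text and table of 9.3.1 and section 9.3.2 all point to 31% plus 20 points, so the 81%/51% line is the lone outlier within each copy of the calculation. One-sided 0.05 is stated in 9.3.1 and again in 15.3.1. The 0.461 sits beside 0.800 as a reported property of the design, so a slipped decimal there has no bearing on N. Section 11's total is plainly a dropped 'per group'. All of that stands, and it limits the point to stated figures.

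It also rules out two stronger readings. A reader might infer that the trial runs at a 46% false-positive rate. It does not: the printed stage sizes and boundaries never exceed 0.0461 at any common rate. A reader might also infer that the trial was sized for a 30-point effect on a 51% placebo rate. It was not: power there is 0.989, so 80 per group cannot come from those inputs with an 80% power target.

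Nor is 51/31 the only conceivable pair that fits. The printed 0.800 arises almost exactly at 60/40, and 51/31 gives 0.805. It is, however, the only pair in the document that fits.

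Finally, reading the printed level as a maximum over common rates is an inference. The formula in 15.3.4 is a figure not shown. The inference rests on the numerical match: 0.0461 at 50%, against 0.0348 at 31%.

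What the defence does not remove is that the hypothesis inputs and the alpha are contradicted in the section that justifies the trial's size and again in the Outline, and that the boundary wording does affect the operating characteristics.

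**Conclusion.** The point holds as a correction of stated figures. The 81%/51% line contradicts the section's own basis and would call for about 36 per group (exact, single stage). The 0.461 contradicts the stated 0.05 and is ten times the rule's exact maximum of 0.0461. The design is sound: power 0.805 at 51% vs 31%, maximum type I error 0.0461, and 100 per group after 20% dropout. These results assume full evaluable numbers of 43 and then 80 per group, independent binomial outcomes, continuation at a difference of at least 2, and success at a difference of at least 11. If success means more than 11, they become 0.762 and 0.033, so the boundary wording has to be settled in the same edit.

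**What to change.** - In section 9.3.1 and the Protocol Outline, replace the expected-rate line with PGA 51%, control 31%.
- In the two-stage table in both places, replace 0.461, 0.800 with 0.0461, 0.80, and add that the significance level is the maximum over the common cure rate, reached at 50%.
- In the Outline's statistical analysis row, section 11 and section 15.3.4, define final success consistently as a difference of at least 11, and continuation to stage 2 as a difference of at least 2.
- In section 11, state 80 per group and 160 in total (100 per group and 200 in total with dropout).

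The cost is a text amendment. Sample size, stage sizes and the tabulated boundaries stay as they are.

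### Sample size: the line stating the expected cure rates gives 81% v 51%, but the stated size, boundaries and power belong to 51% v 31%

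*Protocol*

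**What the plan says.** Protocol Section 9.3.1 gives two incompatible sets of expected cure rates, and the Sample Size row of the Protocol Outline repeats both.

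- **Opening text:** "we assumed that 31% of the cases of CIN 1 would resolve spontaneously, and a clinically significant difference was estimated at 20" per cent. This implies 51% on PGA.
- **Table:** the rows read "Placebo | - | 80 | 31% | 24.8" and "PGA | 1,500mg/day | 80 | 51% | 40.8", the last figure being the expected number of responders. The Korean version of the table in the Outline has the same rates.
- **Line under the hypotheses:** "Expected response rate: PGA Group: 81%, Control Group: 51" per cent. The next line is "significance level : 0.05, statistical power : 80%, one-sided test", followed by "The Sample size is total 160 patients, 80 patients per group when the Single stage method" and "If 20% drop out is considered, the sample is total 200 patients, 100 patients per group".
- **Two-stage table:** 43 per group, then 80 (43+37), with differences in cured patients of +2 and +11 and a power of 0.800.

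Section 9.3.2 reviews published natural cure rates and concludes: "The natural cure rate at 3 months was set at 31.0" per cent. It also takes an effect of at least 20% as the minimum that would justify a larger study.

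**The concern.** The disputed line sits between the hypotheses and the significance level, power and sample size, so it is the formal statement of the alternative for which the trial is sized. It raises the control rate from 31% to 51%, the PGA rate from 51% to 81%, and the target difference from 20 to 30 points.

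Taken literally, it says that the trial expects four in five PGA patients to be cured and that it enrols more than twice the patients needed for 80% power. An ethics committee or regulator could fairly question that. Anyone rechecking the design from this line, or using it to judge how demanding the +11 cut-off is, would get a different size, boundary and power from those printed.

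**Working it through.** **Inputs**

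| Input | Value | Source (Protocol) |
| --- | --- | --- |
| Rates, set A | PGA 51%, control 31% | 9.3.1 text and table; 9.3.2 |
| Rates, set B | PGA 81%, control 51% | 9.3.1, line under the hypotheses; Outline |
| Test | one-sided 5%, power 80% | 9.3.1 |
| Size per group | 43, then 37 more, total 80 | 9.3.1 |
| Stage 1 | stop if the difference is below 2 | 15.3.4 |
| Final | no effect if the difference is below 11 | 15.3.4 |
| Dropout | 20% | 9.3.1 |

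**1. The table's own counts.** 80 × 0.31 = 24.8 and 80 × 0.51 = 40.8, exactly as printed, so the table uses set A. Set B would give 80 × 0.81 = 64.8 on PGA and 40.8 on control. The expected difference in cured patients is 80 × 0.20 = 16 under set A and 80 × 0.30 = 24 under set B.

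**2. Two-stage power, exact.** Let D1 be the PGA-minus-control difference in cured patients at 43 per group, D2 the same difference among the next 37 per group, and D = D1 + D2. Each is a difference of two independent binomial counts. The probability of declaring an effect is P(D1 ≥ 2 and D ≥ 11), obtained by convolving the binomial distributions.

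| Rates (PGA v control) | P(declare effect) |
| --- | --- |
| 51% v 31% | 0.805 (stated power 0.800) |
| 81% v 51% | 0.989 |
| 50% v 50% (no effect) | 0.0461 |

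The last row has the same digits as the 0.461 printed as the significance level in the two-stage table. This supports the reading of the rule used here and suggests that the printed figure has lost a zero, which is a separate slip.

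**3. Single-stage size, normal approximation.** With p̄ the mean of the two rates,

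n = [1.645 √(2p̄(1−p̄)) + 0.842 √(p1(1−p1) + p2(1−p2))]² / (p1 − p2)².

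- Set A: p̄ = 0.41, so n = [1.645 √0.4838 + 0.842 √0.4638]² / 0.04 ≈ 73.7, rounded up to 74 per group.
- Set B: p̄ = 0.66, so n = [1.645 √0.4488 + 0.842 √0.4038]² / 0.09 ≈ 29.8, rounded up to 30 per group.

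With a continuity correction the sizes are 84 and 37.

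**4. Single-stage size, exact.** This is the smallest n at which a cut-off on the difference in cured patients keeps type I error at or below 5% and power at or above 80%. The answer depends on the common rate assumed under the null.

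- Set A: 78 per group with cut-off 11 (null rate 0.41 or 0.50), or 72 with cut-off 10 (null rate 0.31).
- Set B: 36 per group with cut-off 8 (null rate 0.50 or 0.51), or 32 with cut-off 7 (null rate 0.66).

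The stated 80 and +11 are close to set A and far from set B. Even a two-sided test with continuity correction needs only 45 per group under set B.

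**5. Dropout.** 80 / (1 − 0.20) = 100 per group, as stated. This step is the same for both sets.

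**The case against.** The strongest reply is that this is a slip with no operational effect. The decision rule counts cured patients and never uses the assumed rates, so the line cannot change enrolment, the interim decision or the final test. The intended rates can also be recovered: the text and table just above the line, and Section 9.3.2, all point to 31% and a 20-point gain. All of that stands, and the trial is not underpowered. But the line is the formal alternative, it appears in both the Outline and the body, and a reader has to redo the calculation to be sure which pair governs.

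A second reply is that the match to 0.800 depends on how the cut-offs are read. The protocol's wording varies. On continuing after stage 1, the Outline says more than 2 and Section 15.3.4 says two or more. On success, the Outline, Section [11] and Section 15.3.4 all speak of more than 11, although the Outline and Section 15.3.4 declare failure only below 11, which leaves exactly 11 unassigned. If both cut-offs are read strictly (above 2 and above 11), power is 0.753 at 51% v 31% and 0.981 at 81% v 51%. That ambiguity is a separate matter to settle. It does not rescue the 81% v 51% line, which is far from 80% power on either reading.

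It is also fair to note that only the table prints both 31% and 51%. The text and Section 9.3.2 give 31% and a 20-point effect, from which 51% follows.

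**Conclusion.** The concern holds. The line giving 81% and 51% is wrong as written: it contradicts the text and table of its own section and Section 9.3.2, and it does not lead to the stated size or power. None of the natural cure rates cited in Section 9.3.2 (31%, 28%, about 49% at 6 months, 38.8%) reaches 51%, and no source is given for 81%.

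At the planned 43+37 per group, power is 0.805 under 51% v 31% and 0.989 under 81% v 51%. Single-stage sizes for 80% power are 72 to 84 per group under the first pair and 30 to 37 under the second, across the one-sided methods shown. These results assume independent binomial outcomes and equal groups; the two-stage powers also assume cut-offs of at least 2 and at least 11.

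The error lies in the stated assumption, not in the design. It should be corrected because it misstates the hypothesis on which the trial is sized.

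**What to change.** In Section 9.3.1 and in the Sample Size row of the Protocol Outline, change the expected response rates to 51% for PGA and 31% for control. Keep 80 evaluable and 100 enrolled per group, the 43+37 stages and the +2/+11 cut-offs, which belong to those rates.

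The cost is one line of wording in two places, with no change to patient numbers, the decision rule or trial conduct. The same edit is a convenient moment to check the printed 0.461 and to word the cut-offs identically throughout, but neither is needed to resolve this point.
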